The specific Read code lists for extracting comorbidities are being developed using existing published lists of codes including clinicalcodes.org, CALIBER, NHS Scotland’s Information Services Division, and conditions incentivized under the Quality and Outcomes Framework, and new lists drawn from all possible codes within CPRD. Two clinicians will review each set of codes and, when disagreement is present, additional input from the other two clinicians will be used. Additionally, an estimate of the general population prevalence of the comorbidity will be calculated using the selected codes and a sample of CPRD data, and compared with previous epidemiologic studies. See Appendix 3 for sample code lists for hypertension, asthma, and heart failure.

1. **Study Type**

*Specify whether the study will be primarily descriptive, exploratory, hypothesis testing or a methodological piece of research.*

Primarily a descriptive cross-sectional and retrospective cohort analysis.

1. **Study Design**

*Describe the overall research design (for example, case-control, cohort) and reasons for choosing the proposed study design.*

To meet our primary objective of describing the epidemiology of multimorbidity, we will use a cross-sectional design. We will take a random sample of 425,400 patients registered to English General Practices that have provided “research standard” data continuously from January, 2012 until December, 2015. All adult patients (≥18 years of age) from practices meeting this acceptable data quality criteria and who have been registered for at least 12 months prior to January 1, 2012 will be included to create a random sample of 425,400 patients.

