To meet our secondary objective of investigating health service utilisation in multimorbid patients, we will use a retrospective cohort design. We will create a cohort of patients beginning on January 1, 2012 and following these patients over four years until December 31, 2015. The exposed group will be all patients who have multimorbidity as of January 1, 2012, and the unexposed group will be patients who do not have multimorbidity. We will look at the relationship between the exposure of multimorbidity and the outcome of health service utilisation, which will be assessed based on number of GP consultation, number of prescription medications, and number hospital admissions over the four-year follow-up period. This study design will help us account for the effect of differential mortality that may potentially occur between the exposed and unexposed groups. Mortality will be a secondary outcome in our four-year follow-up. Any patients who have transferred out of their practice during the follow-up period will be censored.

1. **Sample Size**

*Please provide an estimate of sample size, and, where possible, a formal power calculation. An estimate of the expected number of patients available in the CPRD database should normally be included.*

For our primary objective of describing the prevalence of multimorbidity, we have calculated a sample size estimate of 425,400 patients.

This sample size calculation was obtained using the following formula for calculating sample size in cross-sectional studies of prevalence^21^.

$$n=\frac{Z^{2}P\left( 1-P \right)}{d^{2}}$$

In this formula, *n* is the sample size and Z is the test statistic corresponding to a 95% confidence level. P is the expected prevalence of multimorbidity. We set P to be 23.2%, which was the prevalence of multimorbidity obtained by the Barnett *et al.* study on a similar population in Scotland^4^. *d* is the precision of the estimate, corresponding to the effect size. We set size *d* to be 0.13%, which was based on the 95% confidence intervals of the prevalence of multimorbidity from the Barnett, *et al* paper^4^*.*

Using the LSOA “Linked Source Data”, we observed that there are currently 95.2% English patients who have patient level IMD data.  We therefore increased our sample size from 405,000 to 425,400 to account patients who will have to be dropped due to missing IMD data.

1. **Data Linkage Required (if applicable)**

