**Appendix 1: List of the 36 disease conditions to be included in multimorbidity count**

| Code | Condition | *Criteria* |
| --- | --- | --- |
|  |  |  |
| HYP | Hypertension | *Read Code ever recorded* |
| DEP | Depression and Anxiety | *Read code recorded in last 12 months OR >=4 anti-depressant prescriptions (excluding low dose tricyclics) in last 12 months OR >=4 anxiolytic/hypnotic prescriptions in the last 12 months* |
| PNC | Painful condition | *>=4 POM analgesics in last 12 months OR >= 4 specified anti-epileptics in the absence of an epilepsy Read code in last 12 months* |
| AST | Asthma (currently treated) | *Read code ever recorded AND any asthma prescription in the last 12 months.* |
| CHD | Coronary heart disease | *Read Code ever recorded* |
| DIB | Diabetes | *Read Code ever recorded* |
| THY | Thyroid disorders | *Read Code ever recorded* |
| RHE | Rheumatoid arthritis, other inflammatory polyarthropathies & systematic connective tissue disorders | *Read Code ever recorded* |
| HEL | Hearing loss | *Read Code ever recorded* |
| COP | COPD | *Read Code ever recorded* |
| IBS | Irritable bowel syndrome | *Read code ever recorded OR ≥ 4 prescription only medicine antispasmodic prescription* |
| CAN | New diagnosis of cancer in last five years | *Read code first recorded in last 5 years* |
| ALC | Alcohol problems | *Read Code ever recorded* |
| OPS | Other psychoactive substance misuse | *Read Code ever recorded* |
| CON | Constipation (Treated) | *≥4 laxative prescriptions in last year* |
| STR | Stroke & transient ischaemic attack | *Read Code ever recorded* |
| CKD | Chronic kidney disease | *Best of the last 2 GFR readings <60* |
| DIV | Diverticular disease of intestine | *Read code ever recorded* |
| ATR | Atrial fibrillation | *Read code ever recorded* |
| PVD | Peripheral vascular disease | *Read code ever recorded* |
| HEF | Heart failure | *Read code ever recorded* |
| PRO | Prostate disorders | *Read code ever recorded* |
| EPI | Epilepsy (currently treated) | *Read code ever recorded AND antiepileptic prescription in last 12 months* |
| DEM | Dementia | *Read code ever recorded* |
| SCZ | Schizophrenia (and related non-organic psychosis) or bipolar disorder | *Read code ever recorded/recorded in last 12 months OR Lithium prescribed in last 168 days* |
| PSO | Psoriasis or eczema | *Read code ever recorded AND ≥ 4 related prescriptions in last 12 months (excluding simple emollients)* |

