**Amendment 4**

The following amendment is proposed, as of 5/12/2019:

Our application of latent class analysis in age strata to determine multimorbidity clusters has revealed many clusters which we wish to understand better.

Data/Statistical Analysis

Subsequent to the identification of clusters of multimorbid patients using latent class analysis and a list of ~40 conditions, we wish to further characterise these clusters in the following ways:

1. Describing **the prevalence of 308 fine-grained conditions** within these clusters (e.g. prevalence of lung cancer, not just cancer). This will be a descriptive analysis using the 308 conditions defined here: <https://www.caliberresearch.org/portal/phenotypes/chronological-map>
2. **Which conditions are recorded first?** Our existing clusters are based on the prevalence of conditions in 2012, defined in the following way: <https://www.phpc.cam.ac.uk/pcu/cprd_cam/codelists/v11/> . We will begin with a simple descriptive analysis of which diseases within a cluster are (on average) recorded first. After this we may try and calculate for each cluster pairs of conditions (A and B) where A more often comes after B, and the relative risk of B given A happening earlier using the approach of Jensen et al., (2014) Nat Comm.
3. **Which causes of death are associated with each cluster?** We will use perform a descriptive analysis of primary cause of death for each cluster
4. **Can we improve identification of multimorbid individuals through the use of linked HES data?** While we have used HES linkage to look at hospitalisation, we have not used it to identify the diseases an individual has. This made sense from the point of view of studying the GP perspective on multimorbidity, but there will be some patients who receive diagnoses in secondary care that do not get entered into GP records. We will use existing HES definitions from <https://www.caliberresearch.org/portal/phenotypes> . We will assess the prevalence of each of the broad disease areas (from the original protocol) and whether it increases with the addition of HES-only diagnoses. We may also repeat the Latent Class Analysis to see how/if results change.

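### Practice data must meet the research standard only from January 2012, yet exposure on 1 January 2012 is read partly from 2011 records that no quality rule covers

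*Protocol*

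**What the plan says.** Four rules in the protocol bear on this point.

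- **Practice rule (Study Design).** English practices are eligible if they supplied research-standard "data continuously from January, 2012 until December, 2015". No earlier start is required.
- **Patient rule (Study Design).** Adults are included "who have been registered for at least 12 months prior to January 1, 2012". This concerns registration, not the quality of the practice's records.
- **Exposure and follow-up (Study Design).** "The exposed group will be all patients who have multimorbidity as of January 1, 2012". Outcomes are then counted by "following these patients over four years until December 31, 2015".
- **Condition definitions (Appendix 1).** Several conditions need recent activity. Asthma requires "Read code ever recorded AND any asthma prescription in the last 12 months", and constipation requires "≥4 laxative prescriptions in last year".

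The index date of the primary, cross-sectional prevalence is not stated outright. The Study Design registration rule is anchored on 1 January 2012, and Amendment 4 says "Our existing clusters are based on the prevalence of conditions in 2012". The Study Population section instead describes adults registered on or before 31 December 2015.

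**The concern.** The quality window protects the outcomes for 48 months and the exposure for none. At 1 January 2012 every Appendix 1 criterion looks backward, into a period for which the practice need not have met the standard. The authors evidently saw that a 12-month look-back was needed, because they require it of patients, but they did not require it of practices. Registration shows that a patient was on the list in 2011. It does not show that the practice's 2011 prescribing and coding were complete.

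If some 2011 records are incomplete, a patient can fall short of a prescription count, lose a condition, and drop below two morbidities into the comparison group. That would tend to dilute the contrast in consultations, prescriptions, admissions and mortality. It would also lower the morbidity count used in the utilisation regressions. If the prevalence is taken at the same date, it would tend to be understated, and a larger sample would not remove such a bias.

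**Working it through.** **1. The plan's own sample size figure.** Inputs from the Sample Size section: P = 0.232, d = 0.0013, Z = 1.96, IMD completeness 95.2%.

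- n = Z²P(1−P)/d² = 3.8416 × 0.232 × 0.768 / 0.00000169 ≈ 405,018, against 405,000 stated.
- 405,000 / 0.952 ≈ 425,420, against 425,400 stated.

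Both reproduce. The issue here does not touch this calculation, but d gives a yardstick for it.

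**2. Windows side by side, for an index date of 1 January 2012.**

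| Element | Period needed | Practice quality required |
| --- | --- | --- |
| Outcomes | January 2012 to December 2015 | Yes, all 48 months |
| Seven conditions with a 12-month or last-year window (DEP, PNC, AST, CON, EPI, PSO, MIG) | Calendar 2011 | None |
| SCZ | Ambiguous: ever or last 12 months, or lithium in the last 168 days | None |
| CAN | 2007 to 2011 | None |
| Other conditions (mostly a Read code ever recorded) | Whole prior record | None |

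SCZ is counted only in part, because its row can be read as satisfied by a code recorded at any time.

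**3. How little error would matter.** Relative under-ascertainment that shifts the prevalence by the full planned precision: 0.13 / 23.2 = 0.56%.

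**4. Illustration on assumed inputs.** Let s be the share of patients in practices below standard in 2011, and r the relative loss of multimorbid patients there. Neither is in the documents. Bias = 0.232 × s × r.

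| s | r | Bias (points) | Multiple of d |
| --- | --- | --- | --- |
| 2% | 5% | 0.02 | 0.2 |
| 2% | 20% | 0.09 | 0.7 |
| 5% | 10% | 0.12 | 0.9 |
| 10% | 10% | 0.23 | 1.8 |
| 20% | 20% | 0.93 | 7.1 |

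The break-even with d is s × r = 0.56%. With s = 2% this needs r = 28%; with s = 20% it needs r = 2.8%. The range runs from negligible to large, and the documents do not say where the study lies in it.

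**The case against.** The strongest case on the other side has four parts.

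**The harm is not documented.** The protocol does not define the research standard, does not say that a practice short of it loses prescriptions, and does not say how many practices reached it late. This stands. It leaves the size open, but it does not close the gap between the rules.

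**Many definitions are robust.** Most conditions have no 12-month window. Asthma and epilepsy need only one recent prescription plus a code, and depression and anxiety can qualify on a recent Read code alone. Patients with frequent prescriptions would clear a threshold of four even with partial capture. This also stands, and it argues against assuming a large loss.

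**The protocol partly deals with it.** The Background compares each condition's prevalence in a CPRD sample with earlier studies. The confounding plan models clustering by practice. The Limitations concede uneven recording and underestimation, and Amendment 4 considers adding hospital diagnoses. None of these addresses the 2011 window or restricts the practices.

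**The direction is not wholly one way.** Painful condition can be met by anti-epileptics when no epilepsy code is present, so a missing code can replace one condition with another. This is a minor qualification.

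A reader might also infer more than the documents support:

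- *That the primary prevalence is certainly affected.* Its index date is not stated. At the end-2015 date in Study Population, the 12-month windows would fall inside the quality period.
- *That the bias is a known multiple of the planned precision.* Any such figure rests on chosen inputs.
- *That regional comparisons are distorted.* This would need late-standard practices to be unevenly spread across regions, which nothing shows.
- *That old cancers entered at registration would count as new under* "Read code first recorded in last 5 years". Nothing in the documents shows that histories are entered and dated that way, and it is a matter of patient registration, not of the practice quality window.

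**Conclusion.** The mismatch is real and certain for the cohort exposure: exposure is fixed on 1 January 2012, seven conditions (and SCZ in part) draw on the 12 months before it, and no practice quality rule covers those months. Some multimorbid patients may be misclassified as unexposed. For the primary prevalence the point is conditional on a 1 January 2012 index date, which is the more natural reading of Study Design and Amendment 4 but conflicts with Study Population.

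The size is unknown. The one firm benchmark is that about 0.56% relative under-ascertainment equals the planned precision; the range of 0.02 to 0.93 points depends entirely on the assumptions of 2–20% of patients in affected practices and 5–20% lower ascertainment there. This is a gap worth closing because closing it is cheap, not because a material bias has been shown.

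**What to change.** In Study Design, require practices to have supplied research-standard data continuously from 1 January 2011 to 31 December 2015, so that the practice rule starts with the 12-month registration rule. Applying the present criterion already needs each practice's quality dates, so no new data item is involved.

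Amendments 3 and 4 show that clustering analyses have already been run. For those, and for any other completed analysis, keep the sample and add a sensitivity analysis restricted to practices that met the standard throughout 2011. Report the number of patients excluded and the change in prevalence and in the exposure contrasts.

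State as a limitation that this does not cover the five-year cancer window or the conditions defined by a code ever recorded, which will still draw on records from before 2011. The index date for the primary prevalence should also be stated, and the Study Population date reconciled with Study Design.

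The cost is that some practices leave the sampling frame, in a number the documents do not give, or that one extra analysis is run. The target sample size does not change.

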1. To use a representative, random sample of a large cohort of adult patients (≥18 years old) registered to an English general practice to describe the epidemiology of multimorbidity by sex, age, ethnicity, socioeconomic status, smoking status, and region.
2. To describe the frequency of pairs of two comorbid conditions in order to identify which morbidities most commonly present together.
3. To describe the relationship between the presence of mental health comorbidities and the number of physical morbidities an individual has.
4. To describe the utilisation of health services by individuals with multimorbidity based on the number of yearly GP consultations, the number of annual prescriptions dispensed, and the number of hospital admissions.
5. To determine patterns of multimorbidity disease combinations associated with health service utilisation outcomes, in order to identify clusters of patients that are in some respect “similar.”
6. **Background**

*Please provide a succinct review of the relevant background literature with references so as to explain the purpose of the study. Please ensure that you refer to any previous research in CPRD that is related, providing published references and, when known, the ISAC Protocol Number.*

The current paradigm for medical research tends to focus single diseases. This prioritisation of the study of individual diseases and treatments often excludes patients suffering from multiple chronic illnesses^2^. However, one of the central components of a strong primary care system is caring for the entire patient rather than focusing on a particular body system or disease^3^. As the UK population ages and more patients develop multiple chronic conditions, management of multimorbidity will become an increasingly important aspect of primary care medicine and research.

The current literature suggests that a substantial part of the population has multimorbidity, and while there are some discrepancies in the estimates of prevalence, these differences may be largely attributed to differences in defining morbidities. In Scotland, Barnett, *et al.*’s 2012 study found that 23.3% of all registered patients age 16 and older had two or more morbidities^4^, while Salisbury, *et al.* (2011) found the prevalence of multimorbidity to be 16% in UK adults^5^. This burden of multimorbidity places large demands on GPs, because it has been reported that multimorbid patients account for 78% of GP consultations^6^.

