The outcome of our descriptive analysis is the prevalence of multimorbidity, and we will define multimorbidity using a list of 36 comorbidities (Appendix 1). See Section D for the rationale for choosing these specific morbidities.

In addition to describing the prevalence of multimorbidity, as part of our descriptive analysis we are interested in the pairing and clustering of different comorbidities. To assess the frequency of the most commonly paired comorbidities, our outcome will be pairs of any two separate morbidities from the code list of 36 comorbidities. Additionally, to evaluate our final descriptive outcome relating to the prevalence of physical-mental health comorbidities, mental health comorbidities will be defined as Depression and Anxiety, Alcohol Problems, Dementia, Learning Disability, and Schizophrenia or Bipolar Disorder. All other morbidities will be defined as physical (See Appendix 1).

*Exposures and Outcomes for Secondary Research Objective:*

Our secondary research objective is to investigate the association between multimorbidity and health service utilisation. The exposure for this four-year retrospective cohort study is multimorbidity, which has been defined above.

We will consider three patient-level health service utilisation outcomes:

- the number of GP practice consultations (in-person or by phone)
- the number of prescriptions a patient has been issued
- the number of hospital admissions.

We will consider mortality as a secondary outcome of the retrospective cohort component of our study.

1. **Data/ Statistical Analysis**

*This section should cover both the analytic methods and also the analyses which are to be performed to meet all the specific aims listed earlier. It is important to ensure that this section is clear and specific about any comparisons which will be made*

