To meet our third aim of examining mental morbidities and the linkage of physical and mental comorbidities, we will report the percentage of individuals with both a physical and mental comorbidity. We will use a logistic regression, controlling for sociodemographic characteristics, to quantify the association between mental and physical morbidities, with the binary outcome being the presence of a mental health comorbidity. We will report odds ratios and covariate adjusted odds ratios of having any mental health disorder based on the number of physical morbidities an individual has. We will also report the odds ratios by sociodemographic characteristics. Additionally, we will use a chi-squared test to assess differences between the prevalence of any multimorbidity and the prevalence of having a physical-mental health comorbidity between our sociodemographic covariates described in Section K.

To meet our fourth aim of describing health service utilisation, we will use the total number of consultations as the denominator to evaluate the proportion of consultations devoted to patients with different levels of multimorbidity. We will also use the mean and standard deviation of the number of consultations and prescriptions to describe consultation and prescribing rates in relation to the number of morbidities. We will calculate the total number of consultations, prescriptions, and hospitalisations a patient has during our four-year study period, and will explore the patterns of the data to determine the most appropriate form of regression to look at the separate relationships between the number of morbidities and the number of consultations, prescriptions, and hospitalisations. In this analysis, we will adjust for patients who died during the four-year follow-up as well as for patients who have been censored due as a result of transferring out of the practice. We will use a Cox proportional hazards model to describe the differences in mortality rate between exposed multimorbidity patients and non-multimorbid patients. All regression analyses will consist of a crude analysis in addition to an adjusted one incorporating the covariates described in Section K.

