| IBD | Inflammatory bowel disease | *Read code ever recorded* |
| MIG | Migraine | *≥ 4 prescription-only anti-migraine prescriptions in last year* |
| BLI | Blindness and low vision | *Read code ever recorded* |
| SIN | Chronic sinusitis | *Read code ever recorded* |
| LEA | Learning disability | *Read code ever recorded* |
| ANO | Anorexia or bulimia | *Read code ever recorded* |
| BRO | Bronchiectasis | *Read code ever recorded* |
| PRK | Parkinson’s disease | *Read code ever recorded* |
| MSC | Multiple sclerosis | *Read code ever recorded* |
| CLD | Chronic Liver Disease and Viral Hepatitis | *Read code ever recorded* |

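### Drug misuse and eating disorders fall on the physical side of the mental/physical split, so Aim 3 misclassifies both its outcome and its predictor

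*Protocol*

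**What the plan says.** The section on exposures, outcomes and covariates draws on the list in Appendix 1: "we will define multimorbidity using a list of 36 comorbidities (Appendix 1"). For the physical–mental analysis it states that "mental health comorbidities will be defined as Depression and Anxiety, Alcohol Problems, Dementia, Learning Disability, and Schizophrenia or Bipolar Disorder". It then closes the list: "All other morbidities will be defined as physical", with a pointer to Appendix 1.

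Appendix 1 has columns for code, condition and criteria, and none that marks a condition as mental or physical. Two of its rows are "Other psychoactive substance misuse" (OPS) and "Anorexia or bulimia" (ANO). Neither is among the five named conditions.

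The third specific aim is "To describe the relationship between the presence of mental health comorbidities and the number of physical morbidities an individual has". The statistical section meets it with a logistic regression whose binary outcome is a mental health comorbidity. It reports crude and adjusted odds ratios of "having any mental health disorder based on the number of physical morbidities an individual has", the percentage of patients with both kinds of condition, and a chi-squared comparison across sociodemographic groups. None of the four amendments changes the split.

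**The concern.** The default rule makes drug misuse and eating disorders physical diseases. This does not fit the rest of the rule: alcohol problems are mental, but misuse of other substances is not. A narrow idea of mental illness cannot explain the gap, because dementia and learning disability are on the mental list.

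Everything in Aim 3 rests on this split. A patient whose only diagnosis is anorexia enters the model with no mental disorder and one physical disease. A patient with depression and bulimia is counted as having physical–mental comorbidity without any physical disease. The reported association would then mix co-occurrence among psychiatric conditions with the link between mental and physical disease. With a sample this large, even a small distortion would carry a very narrow confidence interval.

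**Working it through.** **1. The plan's own figures.** The protocol states no figure for the physical–mental association. The one calculation it gives is the sample size: Z²P(1−P)/d² with Z = 1.95996, P = 0.232, d = 0.0013 gives 3.84146 × 0.178176 / 0.00000169 ≈ 405,003, and 405,000/0.952 ≈ 425,420. These agree with the stated 405,000 and 425,400. Neither uses the mental/physical split.

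**2. Count under the rule.** Appendix 1 has 36 rows. Five are named as mental, so 36 − 5 = 31 are physical, including OPS and ANO. Moving both gives 7 mental and 29 physical.

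**3. What happens to individual patients** (mental disorder / physical count / counted as having both):

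| Recorded conditions | As written | OPS and ANO mental |
|---|---|---|
| Anorexia only | no / 1 / no | yes / 0 / no |
| Depression, bulimia | yes / 1 / yes | yes / 0 / no |
| Drug misuse, COPD | no / 2 / no | yes / 1 / yes |
| Depression, drug misuse, COPD | yes / 2 / yes | yes / 1 / yes |

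The second and fourth types raise the odds ratio as written, because a mental case gains a spurious physical disease. The third type lowers it, because a patient with physical disease is lost from the mental cases. The net direction depends on how common each type is.

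**4. Percentage with both.** Let q be the proportion with OPS or ANO. Let C be any of the five named disorders and P any of the 29 remaining physical conditions. The rule wrongly adds OPS/ANO patients with C and no P, and wrongly drops those with P and no C. So

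written − corrected = q × [Pr(C and not P) − Pr(P and not C)] = q × [Pr(C) − Pr(P)],

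with the probabilities taken among OPS/ANO patients. The figure is overstated if the named mental disorders are more common than other physical disease in that group, and understated if they are less common. It cannot be wrong by more than q. The documents give none of the three quantities.

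**5. Odds ratio per physical condition.** The documents supply no prevalence or association, so all inputs here are assumptions. Each run used 300,000 simulated patients and an unadjusted logistic model.
- Prevalence of the five named disorders: 15%.
- Prevalence of OPS/ANO: 1, 3 or 6%.
- Odds ratio (a) between OPS/ANO and the named disorders: 1, 1.5, 4 or 8.
- Odds ratio (b) of OPS/ANO per other physical condition: 0.8, 1.0, 1.2 or 1.5.
- Odds ratio (c) of the named disorders per other physical condition: 1.0 or 1.4.

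This makes 3 × 4 × 4 × 2 = 96 scenarios. Selected results:

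| q | a | b | c | OR written | OR corrected | Ratio | % both, written | % both, corrected |
|---|---|---|---|---|---|---|---|---|
| 3% | 4 | 1.2 | 1.4 | 1.43 | 1.39 | 1.03 | 9.2 | 9.6 |
| 3% | 8 | 1.0 | 1.0 | 1.07 | 1.01 | 1.07 | 7.6 | 7.2 |
| 3% | 4 | 1.5 | 1.4 | 1.41 | 1.42 | 1.00 | 9.0 | 9.7 |
| 6% | 8 | 0.8 | 1.0 | 1.12 | 0.97 | 1.16 | 8.7 | 7.7 |
| 6% | 1 | 1.5 | 1.0 | 1.00 | 1.17 | 0.85 | 7.0 | 9.9 |

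Over all scenarios the ratio ran from 0.85 to 1.16. With a strong mental link (a = 4 or 8) it ran from 0.93 to 1.16 and exceeded 1 in 39 of 48 scenarios. All nine exceptions had b = 1.5.

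**6. Cross-check of step 4.** In the scenario q = 6%, a = b = c = 1, the written percentage was 7.1. Solving 0.15 × [1 − (1 − p)(0.94)] = 0.071 gives p ≈ 0.44 with at least one other physical condition. The formula then predicts 0.06 × (0.15 − 0.44) = −0.017, and the simulation gave 7.1 − 8.9 = −1.8 points.

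**The case against.** The strongest defence is that the rule is explicit and reproducible. A reader can see which conditions are mental, and five named disorders against everything else is a definable question. Moving two conditions into the outcome changes that question, so part of any gap between the two odds ratios is a change of definition rather than bias. This stands in part. But the protocol promises results for any mental disorder, and even a five-disorder outcome would leave two psychiatric conditions in a count labelled physical. An analysis plan that is not at hand might say more, but the protocol states a closed rule here and leaves nothing open.

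A reader might infer that the Aim 3 odds ratio is inflated, or that the percentage with both is understated. The documents support neither as fact. They give no prevalence or association for OPS or ANO, and the two errors pull in opposite directions. The size also shifts with the assumed inputs. A separate set of runs assumed a mean of 0.7 other physical conditions with overdispersion, a strong mental link and a named-disorder odds ratio of 1.40. It gave 1.42 to 1.50 as written when OPS/ANO had no physical link. With a physical link of 1.5 per condition, the written and corrected values nearly agreed (1.41 v 1.41, 1.42 v 1.41, 1.43 v 1.43, 1.46 v 1.42). All these runs are unadjusted, whereas the protocol also plans adjusted odds ratios.

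A reader might also infer distorted comparisons by age or deprivation. That would need drug misuse or eating disorders to be unevenly spread across those groups, and the documents are silent on this.

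The limit on scope is also fair: Aim 3 is one of five descriptive aims and is not the primary objective.

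**Conclusion.** The concern holds as an unexplained and inconsistent classification. It puts OPS and ANO on the wrong side of the split and so misclassifies the outcome, the predictor and the physical–mental percentage in Aim 3. For the odds ratio, upward bias is the more likely direction if OPS and ANO co-occur with the five named disorders. That condition is plausible but is not given in the documents. Under the assumed inputs the ratio of written to corrected odds ratios was about 0.85 to 1.16, and this range illustrates rather than estimates the error. The percentage with both may be too high or too low, by at most the prevalence of OPS or ANO.

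A shift of a few per cent still matters here. At 405,000 patients the standard error of the log odds ratio was about 0.005 in the simulations, so a 3% shift (ln 1.03 = 0.030) is about six standard errors.

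Nothing outside Aim 3 changes. The multimorbidity count, the 630 pairs and the utilisation and mortality analyses use conditions or totals without the split, as does the clustering by condition in the amendments.

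**What to change.** Add OPS and ANO to the mental health list, giving seven mental and 29 physical conditions. Add a column to Appendix 1 that marks each row as mental or physical, so that no condition is classified by default. Compute the Aim 3 outcome, the physical count, the percentage with both and the sociodemographic comparison on that split. If the 5/31 split is wanted for comparison, for example with earlier work, report it as a sensitivity analysis and state the reason.

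The cost is a short change to the definition, one table column and a rerun of the Aim 3 models. No new data, linkage or patients are needed.
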